### Key words: Vitamin A, Children, Severe malnutrition, Retinol, Retinol binding protein, Diarrhoea, ALRI

**Relevance of the protocol:**

Vitamin A deficiency is an important global health problem including Bangladesh. The problem is greater among under-five children, particularly those malnourished. Vitamin A supplementation reduces morbidity from diarrhoeal diseases and also prevents diarrhoea episodes. On the other hand, there are conflicting reports on the role of vitamin A supplementation on morbidity from acute lower respiratory infections (ALRI) including pneumonia; in non-malnourished children supplementation has actually been reported to be associated with increased ALRI incidence and morbidity. The WHO committee (Underwood et al, 1992) has reviewed both the risk and benefit of mega dose (200,000 IU) vitamin A supplementation during acute illness, particularly diarrhoea, irrespective of the nutritional status of under-5 children (IVACG Policy Statement on Vitamin A, Diarrhoea, and Measles. <http://www.ilsi.org/measles.html> at 1500h on 13 July 2005). In Bangladesh high potency (200,000 IU) of vitamin A is routinely supplemented to under-5 children every 6 months. Absorption of vitamin A precursors from the GI tract is reduced in severely malnourished children, who also lack in retinol binding protein (RBP), required for transportation of retinol to target organs. It can thus be assumed that a significant proportion of supplemented vitamin A is excreted in feces and urine of malnourished children. The excretion of vitamin A substantially increases during acute infections including diarrhoeal diseases. On the other hand, free vitamin A, consequence of reduced RBP, increases their concentration in the body increasing the possibility of adverse events including “pseudotumor cerebri”. It has recently been observed that low-dose daily supplementation of vitamin A to malnourished children produces comparable or better effect on recovery from acute illness and also in preventing infectious diseases among under-five children. However, the studies have limitations such as small sample size, delayed assessment of retinol after supplementation, which needs to be addressed in a well-designed clinical trial. We hope that our proposed study will enable us to compare the efficacy of low-dose daily administration of vitamin A with that of initial mega dose followed by daily low dose of vitamin in children presenting with acute diarrhoeal diseases with or without ALRI. If the results of this study indicate that the daily low-dose has similar efficacy to that of the currently recommended mega dose followed by daily dose of vitamin A that would have important programmatic implications.

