
The national coverage rate (percentage of target age children who received vitamin A capsules during the past six months, according to the mother) of vitamin A in rural areas was 45% in 1982-83[47]. The rate gradually decreased to 37% in 1987-88 and 35% in 1989 respectively [48] [42]. However the Nutritional Surveillance Project reported in December 1995, that the coverage of vitamin A capsule distribution increased substantially and it was 83.6% in rural areas and 73.7% in urban areas [42]. It is noteworthy that night blindness is considered as the marker of vitamin A deficiency, and when that exceeds 1%, is considered as a significant public health problem . In Bangladesh, proportion of children aged 18-59 months having night blindness in rural areas and urban slums were 0.23% and 0.12% respectively. These figures are well below the cut-off for public health significance of vitamin A deficiency. Anecdotal observations of doctors working at the ICDDR,B Hospital, Dhaka, indicate a significant decrease in the number of children with clinical vitamin A deficiency seeking treatment in the hospital. According to a report of the surveillance system of Dhaka Hospital of ICDDR,B 84 children presented with conjunctival xerosis and only three children with keratomalacia/corneal ulcer out of a total of 11605 under-5 children during the period 1996-2004. The children enrolled in our proposed study will receive 5000 IU of vitamin A, and additional 1000 IU during the acute phase and 800 IU during the nutritional rehabilitation phase of severe malnutrition from various diets provided to them during their hospital stay. Thus we estimate that the total amount of vitamin A received from these sources, even after adjusting for urinary excretion and the retinol level, will not fall below the basal and normal requirements. We feel that once we are able to maintain the daily optimal level of vitamin A store in the body the sudden development of keratomalacia can be averted. However, measures will be taken through clinical examination (of eye and skin) to exclude children with any form of clinical vitamin A deficiency at the time of enrollment. Children having clinical vitamin A deficiency disease (conjunctival xerosis, Bitot’s spots, keratomalacia, or dermatosis suggestive of vitamin A deficiency) will not be eligible for enrollment and will be provided with the currently recommended treatment with vitamin A supplementation as is routinely followed in this hospital. It may also be noted that a couple of studies did not observe development of an overt sign of vitamin A deficiency in children not receiving vitamin A (placebo group) [13, 36]. Additionally, serum retinol concentrations were not significantly changed after 7 days of hospitalization both among children receiving the high dose and children receiving the low dose or placebo [13].

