**Study design**

This will be a randomized, double blind, controlled clinical trial examining the effects of daily low dose versus single large dose followed by daily low dose of vitamin A supplementation on the diarrhoea and ALRI/pneumonia morbidities of severely malnourished hospitalized children.

Study site

The study will be conducted at the Dhaka hospital of ICDDR, B. The hospital is located in Dhaka, the capital city of Bangladesh that has a population of over 13 million. Each year, around 100,000 diarrhoeal patients, with and without complications, attend the hospital seeking treatment for their illnesses, and about 6000 of them, mostly under-five children, require admission to the longer stay wards for complications of diarrhoea or presence of other infectious diseases, particularly ALRI/pneumonia and sepsis, and severe malnutrition (45 to 50%).

Inclusion criteria

1. Age 6-59 months
2. Either sex
3. Severe malnutrition as defined by the presence of any of the followings:
   1. Bipedal oedema
   2. Weight (measured after correction of dehydration) for height Z score <-3 of the National Center for Health Statistics (NCHS) reference
   3. Written informed consent of respective parents/ guardians for participation of the children in the study.

Exclusion criteria

1. Failure to obtain consent
2. Received a dose of vitamin A within the last three months
3. History of night blindness or eye signs of vitamin A deficiency
4. Measles or history of measles within last 8 weeks [49]
5. Clinical suspicion of TB (evening rise of temperature, loss of appetite, gradual loss of weight, cough, night sweating) after applying modified Kenneth Jones criteria [50], shock other than due to hypovolaemia or hypoglycaemia, congestive cardiac failure, severe sepsis (hypothermia, tachycardia, tachypnea, hypotension) [51], and seizures disorders
6. Trisomy-21
7. Cerebral palsy
8. Any other known chronic disease (eg. hepatic, renal or congenital disorder) or malignant condition.

Final inclusion in the study

Dehydration would be assessed using a modified WHO guidelines (Dhaka Method)[52] that is routinely practiced at the hospital. Dehydration would be managed using oral or intravenous fluids, as appropriate, following the WHO guidelines. A final diagnosis of acute infection, either diarrhoea or ALRI/pneumonia or both, will be made after the correction of dehydration and patient will be enrolled in the study.

Study Interventions

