There will be two treatment groups: (i) test intervention, and (ii) comparator.

1. Treatment group: Will receive four capsules of vitamin A placebo orally (2 capsules for children aged <12 months) on the day of enrollment plus an oral dose of 5000 IU of vitamin A (in the form of multivitamin drops), and the same oral dose of vitamin A for the next 14 days i.e. throughout their entire nutrition rehabilitation phase in the hospital.
2. Comparator group: Will receive oral mega dose (4 capsules of vitamin A, each containing 50,000 IU i.e. a total of 200,000 IU; 2 capsules for children aged <12 months i.e. a total of 100,000 IU) plus an oral dose of 5000 IU of vitamin A (in the form of multivitamin drops), and the same oral dose of vitamin A for the next 14 days i.e. throughout their entire nutrition rehabilitation phase in the hospital.

A local pharmacutical company (Drug International, Bangladesh) will prepare and supply vitamin A capsules and placebo for the study. One of the investigators will administer the study interventions to the participating children following the randomization schedule at a fixed time of each day, and the date and time of actual administration will be recorded. Randomization will be done by an experienced scientist, not involved in the study in any way, using a block randomization method with variable sizes of blocks between 2 to 6.

Sample size

The sample size of this study has been estimated on expected proportions of clinical success in two groups. Earlier studies have observed 69% and 65% clinical recovery among children suffering from shigellosis and cholera respectively [53, 54], and 60% for pneumonia (personal communication with [name], Kamlapur field site of ICDDR,B) within 48 hours when treated with an effective antimicrobial agent. We assume that the recovery rate would remain same (i.e. 70%) in the high followed by low dose vitamin A group and there would be 15% increase in the rate i.e. 85% in the low dose vitamin A group. Considering 80% power at 5% significance the sample size is estimated as follows:

N = P1 (100-P1) + P2 (100-P2)  F (  ) where P1= 70% and P2 = 85%.

(P1- P2)2

= 118.  = 7.84

Thus the required sample size is 118 in each group, and with an anticipated dropout rate of around 10% the sample size will be 130 children in each of the two treatment groups i.e. a total of 260 children.

Patient recruitment, Clinical and Laboratory Assessments

1. **Patient recruitment**

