   1. Children will be screened for recruitment between 9 am to 4 pm everyday. A trained research assistant will initially screen them. After explaining the study including its aims, procedures, interventions and their possible risks and benefits, rights to refuse participation and withdrawal of consent during study, and confidential handling of information the parents/guardians would require to give consent to enroll their children. The same research assistant will then perform anthropometric measurements including height, weight and mid upper arm circumference, and calculate weight for age, height for age and weight for height percentiles taking National Center for Health Statistics (NCHS) median as the standard. Z-scores will be computed and children with weight for height Z-score less than 3 will be enrolled in the study .
   2. Final enrollment: After rehydration, children will be re-weighed, and final enrollment will be done if weight for height Z-score less than 3 .
2. **Clinical Assessments**
   1. Research assistant will collect the demographic and other data using a pre-designed clinical record form (CRF).
   2. One of the investigators will obtain pertinent medical history and perform through physical examination, and also ensure that the children meet eligibility criteria. All information would be recorded on a pre-designed and pre-tested case report form (CRF).
   3. Randomization: Patient will be randomly assigned to either of the two interventions based on a computer generated randomization table.
   4. During hospitalization data will be collected on the outcome variables as well as relevant clinical information including type and severity of diarrhoea and pneumonia.
   5. All the patients will receive standard treatment as per the hospital’s guidelines.
3. Laboratory assays
   1. **Blood test**s: Blood for retinol and RBP, glucose, complete blood count, serum electrolytes, total protein, albumin and, as measures of infection status, pre-albumin and C-reactive protein (CRP) will be measured after randomization on the admission day. Serum retinol and RBP will also be measured on study day-3 and 15. Any other heamatological test will be repeated if only clinically indicated. . Approximately 3.0 ml of venous blood will be adequate to perform all of the tests.

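### The numbered exclusion list leaves out skin signs of vitamin A deficiency, which the Rationale makes a ground for ineligibility

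*Protocol*

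**What the plan says.** Two places in the Protocol set the rule on clinical vitamin A deficiency.

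The Rationale, after arguing that 5,000 IU daily plus dietary vitamin A should be enough to avert keratomalacia, adds a safeguard: "clinical examination (of eye and skin) to exclude children with any form of clinical vitamin A deficiency". It names four conditions. Three are eye signs (conjunctival xerosis, Bitot's spots, keratomalacia). The fourth is a skin sign, and the sentence runs on: "dermatosis suggestive of vitamin A deficiency) will not be eligible for enrollment". These children are to receive the hospital's routine vitamin A treatment.

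Under Study design, Exclusion criteria, item 3 of eight reads "History of night blindness or eye signs of vitamin A deficiency". It does not mention skin.

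Under Clinical Assessments, one of the investigators is to "perform through physical examination, and also ensure that the children meet eligibility criteria". That step adds no skin criterion of its own. Under Study Interventions, a child in the low-dose group "Will receive four capsules of vitamin A placebo orally" (two capsules if under 12 months), plus 5,000 IU on the day of enrolment and on each of the next 14 days.

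**The concern.** The same child gets two answers. Under the Rationale, a child whose only sign is a dermatosis suggesting vitamin A deficiency is ineligible. Under the numbered list, nothing excludes that child. The list is the only itemised set of criteria against which the investigator's eligibility check can be made, and the fuller rule sits in a background section.

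The omission matters because the exclusion is part of the argument for withholding the mega dose in one arm: children with clinical deficiency are meant to be identified first and treated outside the trial. A child with skin signs only who is enrolled from the list may instead be allocated placebo capsules and the daily low dose.

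**Working it through.** The Protocol states no figure on this point that could be reproduced. The main check is a comparison of text; the arithmetic only sizes the consequence for one child.

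**Step 1. Compare the rule with the list.**

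| Exclusion | Subject | Covers skin signs? |
|---|---|---|
| 1 | No consent | No |
| 2 | Vitamin A dose in the last three months | No |
| 3 | Night blindness history or eye signs | No, eye only |
| 4 | Current or recent measles | No |
| 5 | Suspected TB, certain types of shock, cardiac failure, severe sepsis, seizure disorders | No |
| 6 | Trisomy-21 | No |
| 7 | Cerebral palsy | No |
| 8 | Other known chronic or malignant disease | No; its examples are hepatic, renal and congenital disorders |

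Result: 0 of 8. The nearest candidate is item 8, but a dermatosis first seen at the enrolment examination is not reasonably a known chronic disease. The mismatch also runs the other way: item 3 names a history of night blindness, which the Rationale's list of four conditions does not.

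**Step 2. Look for a later step that closes the gap.** Final inclusion turns on correcting dehydration and diagnosing acute infection. Final enrolment turns on weight-for-height after rehydration. Clinical Assessments provides for a physical examination and an eligibility check but does not make skin signs disqualifying. None of these steps supplies the missing item.

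**Step 3. Supplement received over 15 days** (doses from Study Interventions).

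- Low-dose arm: 15 × 5,000 = 75,000 IU.
- Comparator, 12 months or older: 200,000 + 75,000 = 275,000 IU. Ratio: 75,000 / 275,000 = 0.27.
- Comparator, under 12 months: 100,000 + 75,000 = 175,000 IU. Ratio: 75,000 / 175,000 = 0.43.

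The Rationale also counts 800 to 1,000 IU from diet, read here as per day. Over 15 days that adds 12,000 to 15,000 IU to either arm, so the ratios become:

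- 12 months or older: 87,000 / 287,000 = 0.30 to 90,000 / 290,000 = 0.31.
- Under 12 months: 87,000 / 187,000 and 90,000 / 190,000, both 0.47.

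The comparator arm stands in here for the routine treatment, whose dose the Rationale does not give. The assumption is that this treatment includes at least the mega dose, on the strength of the Relevance section's reference to the "currently recommended mega dose followed by daily dose of vitamin A".

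**Step 4. Chance of the low-dose arm.** Allocation is equal (130 and 130), so the chance is 130 / 260 = 1/2.

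**Step 5. How many children.** The nearest figure in the Rationale is for eye signs among 11,605 under-five children: 84 with conjunctival xerosis and 3 with keratomalacia or corneal ulcer.

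- If the 3 are among the 84: 84 / 11,605 = 0.72%.
- If they are separate: 87 / 11,605 = 0.75%.

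No figure is given for skin signs, so the number affected cannot be computed.

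**The case against.** The strongest reply is that the exclusion is already in the Protocol. The Rationale is current text, its wording is that of a rule rather than background, and the two places can be applied together, because the exclusion list nowhere says that skin signs are acceptable. On this reading the defect is an incomplete transcription. The eligibility check is made by an investigator, is not expressly confined to the numbered list, and uses a case report form that is not shown and may carry the skin item.

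This is fair as far as it goes. Harm does depend on staff working from the list as written. But a numbered list of exclusions is what staff can be expected to apply, and a reader of that list alone cannot know that a further ground exists elsewhere.

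Two objections to the size also stand. The 27% and 43% are the designed contrast between the arms, which applies to every randomised child. They measure the shortfall from routine treatment only under the assumption in Step 3, and the Relevance sentence behind that assumption concerns children with acute diarrhoea, not treatment of clinical deficiency. The 0.72% to 0.75% relates to eye signs, already excluded, in under-five children generally rather than in the severely malnourished children enrolled here, so it may not transfer.

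Finally, the Protocol's own estimate is that the low dose plus diet meets basal and normal requirements, and it cites studies in which placebo children developed no overt sign of deficiency. That limits the concern. It does not remove it, because the Protocol does not present that evidence as applying to children who already have signs.

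**Conclusion.** The concern holds. That the numbered list omits a ground for ineligibility stated elsewhere in the same document is certain from the text and rests on no assumption. The consequence is bounded. It arises only if eligibility is judged from the list, only for children with skin signs and no eye signs or night blindness history, and for such a child it means a one-in-two chance of forgoing the mega dose (200,000 IU, or 100,000 IU under 12 months), provided the routine treatment contains it. Such a child would still receive 5,000 IU daily plus the dietary amount. How many children this concerns is unknown, though probably few. The outcomes, sample size, randomisation and analysis are not affected. The omission should be corrected because it leaves a promised protection for severely malnourished children out of the list that would apply it.

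**What to change.** Reword exclusion criterion 3 along these lines: *history of night blindness, or any eye sign or dermatosis suggestive of vitamin A deficiency*. If the case report form has an eligibility checklist, bring it into line.

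The cost is one phrase. It introduces no new policy, since the Rationale already makes these children ineligible. Recruitment should lose at most a few children, though the Protocol gives no skin-sign figure from which to confirm that. The target of 260 stays as it is.

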**Data Analysis:**

Data will be entered onto personal computer using SPSS statistical package and statistical analyses will be performed using the same program, and z- scores will be determined using Epi Info 2001. Normally distributed continuous variables will be compared by t-test for normally distributed data and Mann Whitney U test will be used for data that are not normally distributed. Time to recovery would be compared by log rank test (Kaplan Mayer survival analysis). Two by two tables will be constructed to relate the findings of discrete variable such as chest X-ray findings of pneumonia (present or absent) and Fisher’s exact test would be performed where indicated. Statistical significance will be set at 5% level.

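### The planned 70% comparator recovery is presented as matching cited rates of 69%, 65% and 60%; at 65% and 60%, 118 per group gives about 74% and 70% power, not 80%

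*Protocol*

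**What the plan says.** All the inputs are in the Sample size section of the protocol. It first gives the evidence on 48-hour recovery under effective antimicrobial treatment: "Earlier studies have observed 69% and 65% clinical recovery among children suffering from shigellosis and cholera respectively", "and 60% for pneumonia (personal communication with" a colleague at a field site). It then sets the planning rate for the comparator: "We assume that the recovery rate would remain same (i.e. 70%) in the high followed by low dose vitamin A group". The effect is expressed as an increase over that rate: "there would be 15% increase in the rate i.e. 85% in the low dose vitamin A group". The error rates follow: "Considering 80% power at 5% significance the sample size is estimated as follows". The result is 118 per group, raised to 130 per group (260 in total) for dropout.

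Two other places bear on this. The Primary outcome list has two separate items, resolution of diarrhoea and resolution of ALRI. Final inclusion in the study admits children with diarrhoea, with ALRI/pneumonia, or with both.

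**The concern.** The wording of the control-rate assumption can only refer back to the three rates just cited, yet none of them is 70% and all are lower. A reader is led to think that 70% is what those data show.

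The choice is not neutral. For a fixed difference, the variance of a proportion shrinks as the rates move away from 50%, so a higher control rate lowers the required sample size. If the true comparator rates are those cited, the trial has less than the stated 80% power for the gain it plans to detect. The gap is widest for pneumonia, which is a primary outcome in its own right.

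This matters for interpretation. The opening statement of relevance says that similar efficacy of the two regimens would have programmatic consequences. A non-significant result from a comparison with about 30% type II error, believed to have 20%, is more easily misread as similarity.

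**Working it through.** **Inputs (all from Sample size).** Factor 7.84 = (1.96 + 0.84)², which implies a two-sided 5% level and 80% power; planning rates 70% and 85%; gain 15 points; cited rates 69%, 65% and 60%; 118 evaluable per group.

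**Step 1: reproduce the protocol's figure.** The protocol's unpooled formula is n = [P1(1−P1) + P2(1−P2)] × 7.84 / (P1−P2)².

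For 70% against 85%: (0.2100 + 0.1275) × 7.84 / 0.0225 = 0.3375 × 348.44 = 117.6, so 118. This agrees with the protocol.

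**Step 2: same formula, same 15-point gain, cited rates as control.**

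- 69% against 84%: (0.2139 + 0.1344) = 0.3483; n = 121.4, so 122
- 65% against 80%: (0.2275 + 0.1600) = 0.3875; n = 135.02, so 136
- 60% against 75%: (0.2400 + 0.1875) = 0.4275; n = 148.96, so 149

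**Step 3: power at 118 per group.** Power = Φ(0.15 / √(V/118) − 1.96), where V is the variance sum from step 1 or 2.

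| Control rate | 0.15 / √(V/118) | minus 1.96 | Power at 118 | Power at 130 |
|---|---|---|---|---|
| 70% | 2.805 | 0.845 | 80.1% | 83.7% |
| 69% | 2.761 | 0.801 | 78.8% | 82.6% |
| 65% | 2.618 | 0.658 | 74.5% | 78.4% |
| 60% | 2.492 | 0.532 | 70.3% | 74.4% |

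The last column takes every randomised child as evaluable. Even with no dropout, 80% is not reached at 65% or 60%. A pooled-variance version gives slightly lower values at 118 (77.9%, 73.5% and 69.4% for the three cited rates), so the result does not depend on the choice of approximation.

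**Step 4: detectable difference at 80% power with 118 per group.** Solve d = 2.8 × √(V/118), where V depends on d.

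- At a 65% control rate, d is about 15.9 points.
- At a 60% control rate, d is about 16.7 points.

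**Step 5: number evaluable per outcome.** Steps 3 and 4 take all 118 per group as having the condition in question. The protocol gives no expected share with pneumonia, so the following shares are assumptions for illustration at 60% against 75%:

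- 80% with pneumonia, about 94 per group: 0.15 / √(0.4275/94) − 1.96 = 0.264; power about 60%
- 50% with pneumonia, 59 per group: 0.15 / √(0.4275/59) − 1.96 = −0.198; power about 42%

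The 70.3% is therefore a ceiling for the ALRI outcome.

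**The case against.** **A sponsor may choose its planning rate, and 70% is close to 69%.** This stands for shigellosis: 70% is ordinary rounding, and the shortfall at 69% is only about 1 point. It does not cover 65% or 60%. Nor does it help to suppose that one overall success rate was meant: any weighted average of the three cited rates lies between 60% and 69%.

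**If 85% is held fixed, power rises.** With control rates of 69%, 65% and 60% against 85%, power at 118 per group is about 84%, 95% and 99% (pooled variance). The arithmetic is right, but the protocol obtains 85% by adding 15 points to the control rate. Holding 85% would imply a 25-point effect in pneumonia, which the protocol does not claim.

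**The practical effect is modest.** In part this stands. The detectable difference moves from 15 to about 16 or 17 points, and the 15 points themselves have no stated source. The stated power is still off by about 5 to 10 points at the two lower rates.

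**Stronger readings that the document does not support.**

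- A reader might infer a calculation error. There is none: 118 follows from the rates entered. The fault is an unsupported input.
- A reader might add the dropout step, since 130 × 0.9 = 117. The protocol says only "with an anticipated dropout rate of around 10% the sample size will be 130 children", and one child per group moves power from 80.1% to 79.8%.
- A reader might take Fisher's exact test as the primary test and deduct further power. Data Analysis says "Fisher’s exact test would be performed where indicated", with chest X-ray findings as the example. It does not assign that test to the primary comparison.
- A reader might average the three rates into one figure near 65%. That assumes equal shares of shigellosis, cholera and pneumonia, and the protocol gives no such case mix.

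**Conclusion.** The point holds as an unsupported and inconsistently stated planning assumption. On the cited rates, the trial does not have the stated 80% power for a 15-point gain. The shortfall at 118 per group is negligible at 69% (78.8%), about 5.5 points at 65% (74.5%) and about 10 points at 60% (70.3%). For diarrhoea the range is about 74–79%. For ALRI it is at most about 70%, and lower to the extent that enrolled children do not have pneumonia.

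This rests on three assumptions: the 15-point difference is the fixed quantity, as the protocol words it; the cited rates are the relevant comparator rates; and the test is two-sided at 5%, as the factor 7.84 implies. It would fall away for any outcome where the sponsor can document a comparator rate of about 70%.

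**What to change.** Rewrite the assumption paragraph in Sample size:

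- Replace the single 70% with the cited rate for each primary outcome (65–69% for diarrhoea, 60% for pneumonia), or give the source and reason for 70%.
- Restate power for a 15-point gain with 118 evaluable per group: about 74–79% for diarrhoea and at most about 70% for pneumonia. Alternatively, state the difference detectable with 80% power: about 15.9 points at a 65% control rate and 16.7 points at 60%.
- Say that these are upper bounds, valid only if all 118 per group have the condition in question, and give the expected number per group with diarrhoea and with pneumonia.

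The cost is one paragraph and a less favourable stated power. No added patients are required. If the sponsor wants to keep the 80% claim at the lower rates, the evaluable numbers are 136 per group at 65% and 149 at 60%, counted among children with the condition.

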With the above background, we propose a study to examine the effects of daily low dose vitamin A (5000 IU for 15 days) in severely malnourished children, aged 6-59 months, with diarrhoea, with or without pneumonia, and compare that with initial high dose (200,000 IU) followed by a daily low doses (5000 IU for 14 days) of vitamin A in a randomized, controlled clinical trial. All children enrolled in the study would receive the standard care and treatment for their diarrhoea and associated illnesses. Serum concentrations of retinol and retinol binding protein will be measured in study children before randomization, after 48 hours (i.e. on 3rd day) and 14 days later (i.e. on 15th day). The duration of diarrhoea, and proportion of children recovering from pneumonia (return of respiratory rate to normal, and resolution of fever, and ability to eat and drink well) within 48 hours will be the primary outcome measures, and the findings would be correlated with serum retinol and retinol binding protein. We hope that this study might provide valuable information in defining an evidence-based programme for vitamin A supplementation to severely malnourished children.

DESCRIPTION OF THE RESEARCH PROJECT

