**Primary outcome**

1. Resolution of diarrhoea
2. Resolution of ALRI

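### The 80% power behind 118 children per group does not carry over to ALRI resolution, a primary outcome that exists only in children who have ALRI

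*Protocol*

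**What the plan says.** The Sample size section rests on one comparison: "The sample size of this study has been estimated on expected proportions of clinical success in two groups". The inputs are a comparator rate, "We assume that the recovery rate would remain same (i.e. 70%) in the high followed by low dose vitamin A group", and a test-arm rate, "there would be 15% increase in the rate i.e. 85% in the low dose vitamin A group", with 80% power and 5% significance. The result is "Thus the required sample size is 118 in each group", raised to 130 per group (260 in total) for about 10% dropout. The same section cites 48-hour recovery of 69% for shigellosis, 65% for cholera and 60% for pneumonia.

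The Primary outcome section lists two items: resolution of diarrhoea and "Resolution of ALRI". The Clinical success definitions give each illness its own 48-hour criterion and define no combination of the two.

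On who is enrolled, the protocol has two versions. Final inclusion in the study says: "A final diagnosis of acute infection, either diarrhoea or ALRI/pneumonia or both, will be made after the correction of dehydration". The Project Summary describes severely malnourished children "with diarrhoea, with or without pneumonia", and the statement of relevance at the front agrees with the Summary. No quota or expected share of children with ALRI appears anywhere.

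The Data Analysis section adds: "Statistical significance will be set at 5% level".

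**The concern.** The calculation treats all 118 evaluable children per arm as the denominator of one tested proportion. The listed outcomes do not have that structure. A child without ALRI cannot resolve ALRI, and both descriptions of the study population admit such children. The ALRI comparison therefore has fewer than 118 children per arm, by an amount the protocol does not state. It also starts from a cited recovery rate below the 70% used.

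The hypothesis claims better recovery from both diarrhoea and pneumonia. If the ALRI comparison is null, a reader who relies on the stated 80% may take it as fair evidence of no difference. That matters here because the protocol says that finding similar efficacy would have programmatic implications.

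**Working it through.** **Inputs.** From the Sample size section: 70% and 85%; 60% for pneumonia; multiplier 7.84 = (1.96 + 0.84)², so two-sided 5% and 80% power; 130 per arm less 10% dropout = 117 evaluable. Assumed, because the protocol gives no figure: the share f of children with ALRI.

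**1. Reproduce the plan's figure.** n = [P1(100−P1) + P2(100−P2)] / (P1−P2)² × 7.84 = (2100 + 1275)/225 × 7.84 = 15 × 7.84 = 117.6, i.e. 118. This matches. A pooled-variance test gives 121 per arm, and 79.2% power at 118, so the choice of formula is immaterial.

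**2. Power for ALRI at 70% vs 85%.** Same unpooled normal approximation, with n = 117 × f per arm: power = Φ(0.15/√(0.3375/n) − 1.96), where 0.3375 = 0.70×0.30 + 0.85×0.15. For f = 0.5, n = 58.5, the standard error is 0.0760, the ratio is 1.975, and the power is Φ(0.015) = 51%.

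**3. Power for ALRI at 60% vs 75%.** This uses the cited pneumonia rate with the same 15-point gain. The variance term becomes 0.60×0.40 + 0.75×0.25 = 0.4275.

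| ALRI share (assumed) | n per arm | 70% vs 85% | 60% vs 75% |
|---|---|---|---|
| 30% | 35 | 33% | 27% |
| 50% | 58.5 | 51% | 42% |
| 70% | 82 | 65% | 55% |
| 90% | 105 | 75% | 65% |
| 100% (118) | 118 | 80% | 70% |

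The last row does not depend on the share. At 60% vs 75% the protocol's formula requires (2400 + 1875)/225 × 7.84 = 19 × 7.84 = 148.96, i.e. 149 per arm with ALRI (152 with the pooled test).

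**4. Diarrhoea.** If every child has diarrhoea, the outcome has 117 to 118 per arm and about 80% power at 70% vs 85%. If children with ALRI only are enrolled, it has less, again by an unstated amount.

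**5. Two outcomes together, which depends on a decision rule the protocol does not give.**
- A win on either at 5%: family-wise error is 1 − 0.95² = 9.75% under independence, and at most 10%.
- Both must succeed: the 5% error holds, but joint power is 0.80 × 0.80 = 64% under independence, even if each outcome had its full 80%.
- Testing one outcome at 2.5% with all 118 children at 70% vs 85%: 71% power.

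**The case against.** Four objections deserve weight.

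*A single combined outcome may be intended.* The primary aim under Specific Aims speaks of one proportion of children resolving diarrhoea and ALRI, and the definitions of success for both illnesses sit under one heading. On that reading 118 fits one test in every child. But the Primary outcome section numbers the two separately, the definitions give two criteria and no combination, and the Project Summary names a different measure for each: duration of diarrhoea, and the proportion recovering from pneumonia. The passages conflict, and the combined reading is not established. Nor would it rescue the 70% and 85% automatically. Suppose 70% diarrhoea and 60% pneumonia recovery, independent, with all children having diarrhoea and 30% to 70% having both illnesses. A child with both then succeeds with probability 0.42, so comparator success is 62% to 50%, and a 15-point gain with 117 per arm has about 71% to 65% power.

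*Multiplicity belongs in the SAP.* This stands. A reader might infer that the 5% error rate is broken. The protocol does not support that: the 5% level is a general statement, nothing says that a win on either outcome suffices, and a SAP not seen here may supply the rule. But no SAP rule can restore children missing from the ALRI denominator when the total is fixed at 260.

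*Diarrhoea is close to universal.* A reader might also infer that both primary outcomes lose power. Under the Project Summary and the statement of relevance, diarrhoea loses none. Only the Final inclusion wording opens that possibility, and it gives no numbers.

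*The ALRI share is assumed.* True. At 90% and the 70% vs 85% rates the loss is only about 5 points. The size is therefore a range, and a blanket claim of severe underpowering goes too far.

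**Conclusion.** The point holds for ALRI. The 118 per group is correctly computed, but 80% power applies only to a 70% vs 85% comparison in which every evaluable child counts, and ALRI resolution is not such a comparison. Its power is about 33% to 75% at 70% vs 85% for assumed ALRI shares of 30% to 90%. At the protocol's own pneumonia rate with a 15-point gain it cannot exceed about 70% with 118 per arm. That last figure rests only on the cited 60% and on keeping the same absolute gain.

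The consequences for error rate and joint power are conditional: error up to 10% if either outcome suffices, or 5% error with about 64% joint power (independence assumed) if both are needed. It should not be stated as fact that the 5% level fails or that diarrhoea is underpowered.

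**What to change.** Reconcile the statement of relevance, Project Summary, Specific Aims, Final inclusion, Sample size, Clinical success and Primary outcome sections on who is enrolled and what is primary. Then take one of two routes.

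1. **One primary outcome that matches the calculation.** For example, diarrhoea resolution at 48 hours, with ALRI resolution secondary. If a combined outcome is preferred, define it in the Primary outcome section and recompute its power, since 70% and 85% need not apply.
2. **Keep both.** Replace the single 80% statement with the power for each outcome in its own expected denominator, using the 60% rate for pneumonia and stating the expected ALRI share. Say whether either outcome suffices (with Holm's procedure) or both must succeed.

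Both routes change wording only and need no extra patients. The price is a stated ALRI power that looks less favourable, or ALRI moving to secondary status. Restoring 80% for ALRI would be a different decision: at an assumed 50% share and 70% vs 85%, 118/0.5 = 236 evaluable per arm, and 236/0.9 gives 263 enrolled per arm, or 526 in total against 260 planned.
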